## Abstract

**Background:**

In many low income countries, the majority of acutely malnourished children are either brought to the health facility late or never at all due to reasons related to distance and associated costs. Integrated community case management (iCCM) is an integrated approach addressing disease and malnutrition through use of community health volunteers (CHVs) in children under-5 years. Evidence on the potential impact and practical experiences on integrating community-based management of acute malnutrition as part of an iCCM package is not well documented. In this study, we aim to investigate the effectiveness and cost effectiveness of integrating management of acute malnutrition into iCCM.

**Methods:**

This is a two arm parallel groups, non-inferiority cluster randomized community trial (CRT) employing mixed methods approach (both qualitative and quantitative approaches). Baseline and end line data will be collected from eligible (malnourished) mother/caregiver-child dyads. Ten community units (CUs) with a cluster size of 24 study subjects will be randomized to either an intervention (5 CUs) and a control arm (5 CUs). CHV in the control arm, will only screening and refer MAM/SAM cases to the nearby health facility for treatment by healthcare professionals. In the intervention arm, however; CHVs will be trained both to screen/diagnose and also treat moderate acute malnutrition (MAM) and severe acute malnutrition (SAM) without complication. A paired-matching design where each control group will be matched with intervention group with similar characteristics will be matched to ensure balance between the two groups with respect to baseline characteristics. Qualitative data will be collected using key informant and in-depth interviews (KIIs) and focused group discussions (FGDs) to capture the views and experiences of stakeholders.

**Discussion:**

Our proposed intervention is based on an innovative approach of integrating and simplifying SAM and MAM management through CHWs bring the services closer to the community. The trial has received ethical approval from the Ethics Committee of AMREF Health Africa - Ethical and Scientific Review Committee (AMREF- ESRC), Nairobi, Kenya. The results will be disseminated through workshops, policy briefs, peer-reviewed publications, and presented to local and international conferences.

**Trial registration:**

PACTR201811870943127; Pre-results. 26 November 2018.

**Electronic supplementary material:**

The online version of this article (10.1186/s12889-019-7497-3) contains supplementary material, which is available to authorized users.

## Background

Malnourished children, particularly those with severe acute malnutrition, have a higher risk of death from common childhood illness such as diarrhea, pneumonia, and malaria. Nutrition-related factors contribute to about 45% of deaths in children under 5 years of age [1, 2] The direct relationship between illness and malnutrition in children is well documented and evidence has shown that malnutrition is a factor in more than half of the children who die after the first month of life [2, 3]. Pneumonia, diarrhea and malaria are the leading cause of child mortality and malnutrition contributes to more than a third of all child deaths.

In Kenya, the trends of malnutrition among children under the age of 5 years over the last 15 years is suboptimal with slow improvement. According to estimates from the 2014 Kenya Demographic and Health Survey (KDHS), more than a quarter (26%) of children under five were stunted, 11% were underweight and 4% were wasted. In Northern Kenya counties where the prevalence of malnutrition is high, the prevalence of stunting, wasting and underweight has been consistently higher for a long time.

Despite the evidence, in many developing countries, a myriad of health system bottlenecks and demand-side barriers limit the reach of health and nutrition interventions leaving out many children in need [4, 5]. As a strategy to address these challenges, WHO and UNICEF issued a joint statement in 2004, supporting the clinical management of common childhood illnesses, including diarrhea and pneumonia at community levels [3, 6]. WHO also issued program guidelines for the home management of malaria [7, 8]. In 2012, elements of these community-based services were brought together in a package known as integrated community case management (iCCM), World Health Organization (WHO) and UNICEF also issued a joint statement of iCCM support [9]. The iCCM is a strategy to extend case management of childhood illness beyond health facilities so that more children have access to lifesaving treatments. The strategy also aims to improve equity by reaching the hard-to-reach and underserved segments of the population [10].

Cognizant to global initiative, the Kenyan Government, after elaborate consultations with stakeholders and aligning within its community health strategy, has launched a five-year National Framework and Plan of Action for Implementation of iCCM in 2013 [11]. The iCCM strategy encompasses the community treatment of malaria, pneumonia and diarrhea by trained and properly supervised community health volunteers [11, 12]. The strategy also involves some aspects of maternal, child health and nutritional screening for children under 5 years and referral of cases of malnutrition to health facilities for further management.

Research evidence has shown that about 80% of children with severe acute malnutrition (SAM) who have been identified through active case finding, or through sensitizing and mobilizing communities to access decentralized services themselves, can be treated at home [13, 14]. Thus, integration of management of acute malnutrition with iCCM would have the potential to maximize synergy of the interventions and improve efficiency of resource utilization.

However, provision for home or community-based management of acute malnutrition is not included as part of the Kenyan iCCM framework. Furthermore; little is known whether the value obtained from integrating the management of acute malnutrition within iCCM is worth the resources invested in the implementation of this intervention program. Evidence on the potential impact as well as practical experiences on how to integrate nutrition (including community-based management of acute malnutrition) as part of an iCCM package is limited or scantly documented.

Therefore, we aim to test the feasibility and effectiveness of integrating management of acute malnutrition (both MAM and SAM) into iCCM including treatment outcomes, CHVs performance, and coverage elucidating the enabling factors and challenges of integration. Such local evidence could inform policy and strategies for scaling up effective coverage of nutrition interventions, and therefore will have a paramount significance in informing the potential impact, costs and cost-effectiveness of linking nutrition with iCCM in Kenya.

### Research questions

#### Primary research question

The primary research question that the study seeks to answer is: Does integrating management of acute malnutrition (including MAM and SAM) into iCCM improve coverage, quality of care, and treatment outcomes of children 6–59 months with acute malnutrition?

#### Secondary research questions

The study will also explore a number of secondary research questions focusing on the process variables. The secondary research questions include:
Can CHVs effectively manage acute malnutrition at the community level?
To what extent can CHVs screen, give treatment and manage ready-to-use therapeutic food (RUTF), ready-to-use supplementary food (RUSF) and other iCCM commodities at community level?What are the experiences of the CHVs in using the simplified CMAM tools?What is the effect of integrating acute malnutrition on the CHV’s performance, in regards to workload and quality of care in the management of primary iCCM illnesses (diarrhea, malaria, and pneumonia)?What are the enabling factors and challenges in integrating management of acute malnutrition into iCCM?Is the integration of management of acute malnutrition into iCCM cost effective compared to the baseline system (traditional facility-based approach)?

### Conceptual framework and operationalization

This implementation research seeks to test the conceptual theory of change as shown in Fig. 1 Under the iCCM, we argue that an effective training of CHVs to screen, treat malnutrition combined with an adequate provision of commodities: RUTF, RUSF, adequate supportive supervision will trigger a timely case-finding of MAM/SAM cases which will result to an early treatment to uncomplicated cases of malnourished children, hence increased treatment coverage. Furthermore, a full adherence of the CHVs and individuals to the treatment protocol will yield a high recovery rate, little defaulting and reduced case-fatality rate.

**Fig. 1 Fig1:**
[figure not shown]
Study’s conceptual framework

## Methods/Design

### Study design

This is a two-arm, parallel groups, Cluster Randomized Controlled Trial (CRCT) implementation study. The intervention arm involves deployment of CHVs trained to screen, diagnose and treat moderate acute malnutrition (MAM) and severe acute malnutrition (SAM) in to ten randomly selected clusters (CUs); while in the control arm, CHVs will provide the standard of care that include screening and referral of MAM/SAM cases to the nearby health facility for treatment by healthcare professional. An independent trial steering committee and a national level technical advisory committee (TAG), will oversee the trial, review progress, and decide on any changes to the protocol. A study statistician will also provide data advice to the trial steering committee, as necessary.

### Study setting

This trial will be conducted in Turkana and Isiolo Counties of Northern Kenya. The sites were identified based on a pre-set criteria including, but not limited to:
High burden of acute malnutrition in the area. Being arid and semi-arid lands (ASALs), both Turkana and Isiolo Counties have high prevalence of acute malnutrition. This will make it possible to get adequate sample size and also provide opportunity for CHVs to practice and gain experience in case management.Long distances to health facilities; thus, justifying community case management of acute malnutrition.Existence of community units (CUs) with CHVs that have already been trained on the basics of community health strategy modules.A supportive County Government and where the county health management team (CHMT) has clear plans for rolling out the community health strategy. Both Turkana and Isiolo CHMTs have identified iCCM and CMAM as priority interventions in their areas.Preferably where there is existing supply chain system for RUTF and RUSF established through a partnership between the County Government and UNICEF, World Food Program (WFP) and Kenya Medical Supplies Authority.Presence of Action against Hunger (ACF), Save the Children, or UNICEF within the county to supplement the Ministry of Health (MoH). Apart from reducing the operational costs of the research, the on-the-ground presence will make it possible to rapidly roll out the project (without having to spend time on setting up in a new area). Save the Children is active in Turkana while ACF is implementing nutrition programs in Isiolo CountyEasy to access and relatively secure county to enable consistent implementation and ongoing monitoring and evaluation of the project. Ease of access will be critical as some of the project partners such as MoH’s New-born, Child and Adolescent Health Unit (NCAHU), Nutrition and Dietetics Unit (NDU) and KEMRI will be based in Nairobi but expected to be making regular visits to the study sites. Both Counties are accessible either by road or air.

### Description of the counties selected for the trial

#### Turkana County

Turkana County, situated in North Western Kenya, is the largest of the 47 counties in Kenya with a total area of 77,000 Km^2^ administratively divided into seven sub counties namely; Turkana Central, Loima, Turkana South, Turkana East, Turkana North, Kibish and Turkana West. According to the latest, 2009, Kenya Population and Housing Census (KPHS) [15] and statistical estimates, the county has a population of 855,399, and expected to grow to 1,427,797 by the year 2017. The population of children under 1 year and those below 5 years is projected to reach 25,922 and 186,243 respectively by 2017.

Turkana is drought-prone and experiences frequent, successive and prolonged droughts virtually every year. Turkana’s harsh environment and historic underdevelopment has led to the highest poverty rate in Kenya at 94%, with significantly lower indicators for human development and service coverage than the rest of the country. According to the 2009 KPHS, less than one in five (18%) of the population can read and write, only 9% roads were tarmac and less than one in five households had access to improved sanitation [15]. The average distance to a hospital, health centre or dispensary is 50 km. Serious gaps in human resources further complicate service availability. Doctor to population ratio stands at 1:70,000 while nurse to population ratio is 1:5200 [16].

According to the SMART survey conducted in June 2015 covering all the livelihood zones in Turkana county (pastoral, agro-pastoral and formal employment/business/petty trade), about one in four (25%) children in the county are acutely malnourished. The rates of acute malnutrition in Turkana Central/Loima, North and South/East indicated a *very critical* nutrition situation, while the nutrition situation in Turkana West was classified as *critical*. The weighted Global Acute Malnutrition (GAM) for Turkana County was 21.2% and SAM rate was 5%.

#### Isiolo County

Isiolo County is located in the North Eastern part of Kenya and borders Marsabit County to the North, Samburu and Laikipia Counties to the West, Garissa County to the South East, Wajir County to the North East, Tana River and Kitui Counties to the South, Meru and Tharaka Nithi Counties to the South West. The county covers an area of approximately 25,700 km^2^ and has an estimated population of 143,294 of which children aged 0–59 months are estimated to be 31,163. It consists of three sub-counties namely Isiolo, Garbatulla and Merti.

The county is characterized by recurrent droughts, hot and dry climate with low and erratic rainfall patterns, and is prone to food insecurity predisposing vulnerable groups such as children aged 6–59 months to malnutrition. The county has two rainfall seasons; long (mid-March to May) and short rain (October–December) season. The county just like the other ASALs counties has poor child health indicators. The most recent SMART survey reported an increase in fever from 25% in 2015 to 43% in 2016, acute respiratory infection from 58 to 64% and diarrhoea from 16.3 to 25%. Additionally as expected with the high prevalence of child health diseases, the county has poor nutritional indicators. The SMART survey reported a GAM prevalence of 3.8% [95% CI, 2.3%- 6.4] and SAM prevalence of 0.4% [95% CI, 0.1%-1.6]. Isiolo County has weak community health systems structure and these will need to be strengthened as part of implementation of this protocol**.**

Total = 5 CUo (120 children)	Total = 5 CU_I_ (120 children)	Total = 5 CUo (120 children)	Total = 5 CU_I_ (120 children)

CU stands for community units. CUo, CU_I_ are community units in the control and intervention, respectively

### Sampling procedures

Households with a case of MAM or SAM deemed eligible to the survey will be selected using two-stage cluster sampling technique. In the first stage, we will randomly select CUs based on their level of functionality (existence of at least one CHEW, at least one dialogue day in the last 3 months, at least 10 CHVs in the community unit…etc.) and distance to the nearest health facility; where we shall consider a distance of greater than 5 km to the nearest health facility. At the second stage, a random sampling will be used to select the 24 cases of MAM/SAM in each community unit from sampling frame of MAM/SAM diagnosed by CHVs. For instance with regard to Isiolo Sub-County in Isiolo County, 10 CUs are classified as functional and five kilometers from the nearest health facility meanwhile for Loima Sub-County in Turkana County, we have 23 communities units which are classified as functional. Hence, we will randomly select 10 community units in Loima Sub-County using Stata. For Isiolo County the same approach is used to select the 10 community units.

#### Inclusion/exclusion criteria

To be included in the study, the following criteria highlighted in Table 2 should be met.

**Table 2 Tab2:** Inclusion and exclusion criteria

CHVs Inclusion/ exclusion Criteria	Under-five Children Inclusion/ Exclusion Criteria
Inclusion criteria • CHVs who have been recruited and trained as CHVs by the MoH community strategy and willing to undertake and devote more of their time to the study	Inclusion criteria • Children 6 to 59 months presenting with SAM (a MUAC of < 115 mm or presence of bilateral pitting edema, without complications) or MAM (MUAC of 115 to 125 mm). • Parents/caretakers willing to participate in the study
Exclusion criteria • CHVs who have discontinued their community services or move out of the study area	Exclusion criteria • Parents/caretakers who are not willing to consent/ participate in the study.

#### Outcome measures

The overarching our outcomes of integration are seamless service provision, maximized synergy and improved efficiency and effectiveness. The following list shows key primary and secondary outcome indicators.

### Primary outcomes

Cured rateCase-fatality rate/Death rateDefaulted rateNon-cured rateAverage length of stayAverage weight gainCoverage rate

### Secondary outcomes

Treatment of fever, pneumonia and diarrhea.Quality of care (CHVs performance and workload)Challenges and enablers in the effective integration of management of acute malnutrition into iCCMCost-effectiveness analysis
Cost per child recovered (from both a program and a societal perspective)Incremental cost-effectiveness ratio for ICCM modelRange of costs within the sensitivity analysis

### Intervention protocol

#### Criteria for admission

At admission, the CHVs will only screen under five children (aged 6–59 months) and carryout preliminary examination for any danger signs. This will be followed by further examination for complaints including cough/cold, diarrhea, dehydration and fever, which will be followed by anthropometric measurements to classify the child in relation to nutritional status either MAM, SAM or normal. A special five color-band MUAC tape will be used to allow identification.

Children with MUAC < 9.5 cm and/or less than 4 kg on the dosage scale, with/without bilateral pitting oedema, those who fails the appetite test or show presence of iCCM danger signs or other illnesses other than iCCM diseases (diarrhoea, malaria, pneumonia), sick neonates (less than 1 month) and malnourished children less than 6 months, will be subject for referral to the health facility. However, those sick children below 2 months and caregivers who fail to consent will be excluded at the recruitment and only referred to the health facility.

If MUAC is < 11.5 cm, the child will be classified as SAM; before admitting the child directly for treatment, do the following: children presenting a MUAC of < 11.5 cm will be defined as with SAM while MAM will be defined as MUAC of between 11.5 cm and 12.5 cm. The CHVs will then conduct physical examination of MAM and SAM cases. At this stage, examination for any oedema not observed during assessment of danger signs will be detected. Appetite test will then be conducted setting the stage for either referral or exclusion. Wait for up to 30 min before deciding the child has poor appetite. If the child takes significant quantities as indicated in the Table 3, interpret as the child has good appetite. If no complications and good appetite, the child will be admitted for community-based management of malnutrition.

**Table 3 Tab3:** Appetite test interpretation

Weight (kg)	Sachet portion the child needs to finish to pass appetite test
4–6.9	1/4 to 1/3
7–9.9	1/3 to ½
10–14.9	1/2 to ¾
15–29	3/4 to 1

For SAM children, the CHVs will give first dose amoxicillin dispersible tablets (DT) on the spot and twice for 7 days before the next visit. If rapid diagnosis test (RDT) is positive for malaria, CHVs will give one dose on the spot and twice daily for 3 days (the prescriptions will clearly be explained to the mother). Then RUTF will be given to the mother/caregiver and explain the daily intakes throughout until the next visit as explained. Table 4 provides details on RUTF that should be given to children based on their weight.

**Table 4 Tab4:** Dosing chart for RUTF

Child’s weight (kg)	Packets per day	Packets per week
4.0–4.9	2	14
5.0–6.9	2.5	18
7.0–8.4	3	21
8.5–9.4	3.5	25
9.5–10.4	4	28
10.5–11.9	4.5	32
≥ 12	5	35

With regards to MAM cases, albendazole and folic acid (for weight) will be given on the spot and further dosage explained to the mother/caregiver. Then CHVs will give RUSF for the children for 7 days until the next visit. Mother/caregivers will be advised to respect follow-up, breastfeeding and diversification of feeding in addition to RUSF. The CHVs will use the following dosing chart to administer.

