#### Follow-up stage

At follow-up, CHVs will ask and seek for general danger signs and examine any complaints on the child. In addition, the systematic evaluation will be conducted to examine any cough, fever or diarrhea following the standard treatment and follow-up protocol. Anthropometric measurement weight and MUAC will be taken to determine any changes (gains) in the child. The CHVs will further conduct systematic evaluation to look for edema not detected at the general danger signs and appetite test. Children with either danger signs, failed appetite test, weight loss, diarrhea will be referred to the health facility, otherwise the CHVs will conduct treatment for MAMA or SAM as appropriate.

For SAM cases, during follow-up the RUTF will be provided for the next 7 days and if RDT is positive, ACT will be provided on the spot and twice daily for 3 days. Adelbanzole will be given if during the second visit the child is aged more than 12 months. In the case of MAM, the CHVs will give folic acid and continue RUSF for the next 7 days. The diversification and breastfeeding should be emphasized again at this point.

Furthermore, during follow-up all SAM children will be subject to weekly visit to CHVs for MUAC measurement and weight using the dosage scale, and collection of RUTF as per dosage scale will continue for a maximum of eight weekly visits if the child is progressing well, otherwise referral will be recommended in case of non-response to treatment. On the other hand, MAM children will be subject to bi-weekly (every 2 weeks) visits for MUAC measurement and collection of RUSF (1 sachet per day for 16 weeks for a maximum of eight visits if child is progressing well, otherwise the child needs to be referred). Table 5 outlines the follow-up procedure for both MAM and SAM.

**Table 5 Tab5:** Follow-up procedure for both MAM and SAM

Follow up	Discharge criteria		Action
1) SAM, MUAC < 11.5 cm			
Weekly visit to CHV for MUAC measurement and weight using the dosage scale and collection of RUTF as per dosage scale Maximum of 8 weekly visits if child is progressing well Two consecutive MUAC and/or weight measurements with no change or deterioration	cured	MUAC≥12.5 cm 2 consecutive green on MUAC	Discharge as cured
	defaulter	Misses 3 consecutive visits	Exclude from the study, Trace and admit as return defaulters but not for study

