	Treatment failure	Two consecutive MUAC and/or weight measurements with no change or deterioration	Refer to health facility for further investigation
	/Non-response	Two consecutive MUAC measurements with no change of deterioration	
	Lost to follow up	Misses 3 consecutive visits and cannot be traced	Exclude from the study
2) MAM; 11.5 cm ≤ MUAC < 12.5 cm			
Bi-weekly visits (every 2 weeks) for MUAC measurement and collection RUSF (1 sachet per day for 16 weeks Maximum of 8 visits if cyhild is progressing well	cured	MUAC≥12.5 cm 2 consecutive green on MUAC measurement	Discharge as cured
	defaulter	Misses 3 consecutive visits	Exclude from the study, trace and admit as return defaulters but not for study
	Treatment failure/non-response	Two consecutive MUAC measurements with no change; deterioration on MUAC	Refer to health facility for further investigation
	Lost to follow up	Misses three consecutive visits and cannot be traced	Exclude from the study

All the activities during this intervention will be clearly documented using primary data collection tools and will be collated and for further analysis on the effectiveness of ICCM-CMAM integration.

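### The MAM ration is written as 7 days per visit, but MAM visits and RUSF collection are every 14 days

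*Protocol article*

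**What the plan says.** The article gives two sets of instructions for MAM children treated by community health volunteers (CHVs).

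**A 7-day ration.** At admission (Criteria for admission): "Then CHVs will give RUSF for the children for 7 days until the next visit". At follow-up (Follow-up stage, second paragraph): "the CHVs will give folic acid and continue RUSF for the next 7 days".

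**A 14-day interval.** The next paragraph of Follow-up stage states that "MAM children will be subject to bi-weekly (every 2 weeks) visits for MUAC measurement and collection of RUSF", with the dose and cap given as "1 sachet per day for 16 weeks for a maximum of eight visits". The MAM rows of Table 5 repeat this: "Bi-weekly visits (every 2 weeks) for MUAC measurement and collection RUSF (1 sachet per day for 16 weeks Maximum of 8 visits".

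Table 5 also defines MAM outcomes by visits. A defaulter is a child who "Misses 3 consecutive visits". Cure needs two consecutive green MUAC readings, and non-response includes two consecutive readings without change.

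For severe acute malnutrition (SAM), ration and interval agree: 7 days of RUTF and weekly visits.

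**The concern.** A 7-day ration at one sachet a day cannot last to a visit 14 days later, and weekly visits capped at eight cannot fill 16 weeks. A CHV given this text has two ways to resolve it, and each does damage.

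- **Keep the two-weekly visits and hand out 7 days of RUSF.** The child has no supplied RUSF for 7 of every 14 days. CHVs in the control arm only screen and refer, so this instruction acts on the intervention arm. Lower recovery there would work against showing non-inferiority on recovery, the outcome used for the sample size.
- **Keep the 7-day ration and see the child weekly.** The visit cap then ends treatment at half the intended time, and cure, default and non-response are each judged over half the intended time. The rates of cure, default and non-cure and the length of stay are all listed as primary outcomes. The shifts need not all run in one direction, but each would be an artefact of the schedule.

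The two rules also differ twofold in RUSF per child on a full course, which bears on the cost per child recovered, a secondary outcome.

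**Working it through.** **Inputs**
- Ration per MAM contact: 7 days (Criteria for admission; Follow-up stage).
- MAM visit interval: 14 days (Follow-up stage; Table 5).
- Dose: 1 sachet per day for 16 weeks, maximum 8 visits (same places).
- Default: 3 consecutive missed visits. Cure: 2 consecutive green readings (Table 5).
- Acute malnutrition (GAM) and SAM prevalence: Turkana 21.2% and 5%; Isiolo 3.8% and 0.4% (county descriptions).

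**1. The plan's own schedule**
- Duration: 8 visits × 2 weeks = 16 weeks.
- Sachets needed: 16 weeks × 7 days × 1 = 112.
- Sachets supplied at 14 per visit: 8 × 14 = 112.

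The two-weekly rule closes exactly.

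**2. The 7-day ration on that schedule**
- 8 visits × 7 = 56 sachets; 56/112 = 50%.
- With the admission ration counted in addition to eight follow-up visits: 9 × 7 = 63; 63/112 = 56%.
- Within each interval: 14 − 7 = 7 days uncovered.

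**3. Weekly visits instead**

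| Quantity | Two-weekly | Weekly |
|---|---|---|
| Maximum course (8 visits) | 8 × 14 = 112 days | 8 × 7 = 56 days |
| Three missed visits (default) | 3 × 14 = 42 days | 3 × 7 = 21 days |
| Gap between two consecutive readings | 14 days | 7 days |

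Sixteen weeks of weekly visits would need 16 visits, twice the cap.

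**4. Which statement is more likely wrong**

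The two-weekly rule appears twice and its arithmetic closes. The 4-month follow-up under Data collection procedures also fits a 16-week course. Weekly visits are set only for SAM, where they match a 7-day ration. The 7-day MAM wording was therefore probably carried over from the SAM text, though the document does not settle this.

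**5. Children affected**

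This step assumes that the trial's case mix follows the county surveys, whose case definition is not stated.
- Turkana: (21.2 − 5.0)/21.2 = 76%; 0.764 × 120 = 91.7.
- Isiolo: (3.8 − 0.4)/3.8 = 89%; 0.895 × 120 = 107.4.

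That is about 92 to 107 of 120 intervention-arm children.

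**The case against.** The strongest reply is that the texts can be reconciled. Suppose the 7-day rations apply only at admission and at a first follow-up one week later, with two-weekly visits after that. Then 7 + 7 + 7 × 14 = 112 sachets over eight follow-up visits, exactly the 16-week course. The arithmetic is right, but the article nowhere states this schedule. It also needs two one-week intervals at the start, which the two-weekly rule does not allow. It shows that the authors should confirm what they meant; it does not remove the conflict.

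Second, the intended dose is fairly plain, since one sachet a day for 16 weeks implies continuous supply, and trained CHVs may simply follow Table 5. The RUSF dosing chart announced in the admission section is not in the text available here and may give the amount per visit. What CHVs would actually dispense is therefore unknown. This limits any claim about harm, but nothing visible says that Table 5 prevails over the two 7-day sentences.

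Third, the 50% shortfall is for a full course, and children discharged early as cured would need fewer sachets in total. That stands for the totals. The gap of 7 days in every 14 applies for as long as the child is in treatment.

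Fourth, the number of children affected rests on survey prevalences, and the Isiolo SAM figure is imprecise (95% CI 0.1% to 1.6%). That is also fair, but the contradiction does not depend on the number.

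Finally, under-supply would make non-inferiority harder to show, so this scenario does not raise the risk of wrongly accepting CHV treatment. That is true of under-supply. It does not make it acceptable to test the intervention at half its stated ration.

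**Conclusion.** The concern holds. The article states two incompatible supply rules for MAM within the experimental treatment, and nothing else in it resolves them. Followed literally on the two-weekly schedule, the 7-day ration delivers 50% of the stated full course (56% if the admission ration is extra). Resolved through weekly visits, it halves the maximum course from 112 to 56 days and the default window from 42 to 21 days.

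Confidence in the contradiction is high. The effect on recovery cannot be derived from the document. That most intervention-arm children would be affected rests on the survey case-mix assumption. The sample size is not touched. The point should be fixed before CHVs are trained, because it governs both the dose delivered and the timing of primary outcomes.

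**What to change.** In the MAM sentences of Criteria for admission and Follow-up stage, change the ration from 7 to 14 days and state 14 sachets per visit. Eight visits then supply 112 sachets, in agreement with Table 5.

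If weekly MAM visits are intended, change the interval and the eight-visit maximum in Follow-up stage and Table 5 instead, and revise the visit-based definitions of cure, default and non-response to match. If an early first visit at one week is intended, state it, with the ration for each contact.

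The cost is two sentences and the CHV job aid on the first option, and a revision of the MAM rows of Table 5 as well on the others. On the first option, sample size and analysis are unchanged.
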